## Abstract

**Background:**

Nigeria’s healthcare system capacity to stem the increasing trend in hypertension is limited in coverage, scope and manpower. Use of trained community-based care providers demonstrated to be an effective complement in improving access to, and supporting healthcare delivery has not been adequately examined for hypertension care in Nigeria. This study is proposed to evaluate the effectiveness of using trained community-oriented resource persons (CORPs) to improve hypertension control in Nigeria.

**Methods:**

An intervention study will be conducted in three states using a mixed method design. First is a baseline survey using a semi-structured pre-tested questionnaire to collect information on demographics, clinical data, knowledge, occurrence and risk factors of hypertension among 1704 adults ≥18 years. Focus group discussions (FGD) and key informant interviews (KII) will be conducted to explore a community’s experience of hypertension, challenges with hypertension management and support required to improve control in 10 selected communities in each state. The second is a cluster-randomized controlled trial to evaluate effect of a package on reduction of blood pressure (BP) and prevention of cardiovascular (CVD) risk factors among 200 hypertensive patients to be followed up in intervention and control arms over a 6-month period in each state. The package will include trained CORPs conducting community-based screening of BP and referral, diagnosis confirmation and initial treatment in the health facility, followed by monthly home-based follow-up care and provision of health education on hypertension control and healthy lifestyle enhanced by phone voice message reminders. In the control arm, the usual care (diagnosis, treatment and follow-up care in hospital of a patient’s choice) will continue. Third, an endline survey will be conducted in both intervention and control communities to evaluate changes in mean BP, control, knowledge and proportion of other CVD risk factors. In addition, FGD and KII will be used to assess participants’ perceived quality and acceptability of the interventions as delivered by CORPs.

**Discussion:**

This research is expected to create awareness, improve knowledge, perception, behaviours, attitude and practices that will reduce hypertension in Nigeria. Advocacy for buy-in and scale up of using CORPs in hypertension care by the government is key if found to be effective.

**Trial registration:**

PACTR Registry PACTR202107530985857. Registered on 26 July 2021.

## Administrative information

Note: the numbers in curly brackets in this protocol refer to SPIRIT checklist item numbers. The order of the items has been modified to group similar items (see http://www.equator-network.org/reporting-guidelines/spirit-2013-statement-defining-standard-protocol-items-for-clinical-trials/).

## Introduction

### Background and rationale {6a}

Hypertension is now recognized as a major contributor to the global burden of diseases and mortality [1, 2]. The prevalence of hypertension is rising globally owing to demographic transition and increase in exposure to lifestyle risk factors including unhealthy diets such as high sodium, low potassium intake and lack of physical activity [3].

An estimated 1.13 billion people worldwide have hypertension with, two-thirds living in low- and middle-income countries [4]. .Estimates suggest that in 2010, 31.1% of adults worldwide had hypertension. The prevalence of hypertension among adults was higher in LMICs than in high-income countries (31.5% versus 28.5%) [3]. In 2015, an estimated 8.5 million deaths were attributable to systolic blood pressure > 115 mmHg, 88% of which were in low-income and middle-income countries [5]. While average age-standardized BP is decreasing in most high-income countries, it is increasing in most low-income and middle-income countries with 32%–50% of adults estimated to be hypertensive in sub-Saharan Africa [3].

Hypertension is a leading risk of death in sub-Saharan Africa causing more than half a million deaths and more than 10 million life years lost. The high prevalence of hypertension and the increasing trend of early onset is a major concern in the development of the region as the young and active workforce population are being incapacitated and worst still depleted. Reports from WHO in 2015 shows the region currently has the highest age- standardized rates of hypertension worldwide with about 46% of individuals aged 25-years and above being hypertensive [6].

In Nigeria, like in most African countries, hypertension is the foundation of cardiovascular disease [7]. In a recent meta-analysis of blood pressure surveys in Nigeria, the documented overall prevalence of hypertension was 28.9% (95%CI, 21.1–32.8%), with a prevalence of 29.5% (95%CI, 24.8–34.3%) among men and 25.0% (95%CI, 20.2–29.7%) among women [8]. There were about 20 million cases of hypertension in the country in the year 2010. This is projected to rise to 39.1 million cases by the year 2030 [8]. Currently, an epidemic of premature cardiovascular mortality and early appearance of hypertension, a risk factor, is being experienced in Nigeria [9, 10]. Studies conducted by our team in two urban communities in Ibadan, which constitutes one of the study sites (Oyo State) for this proposed study, found prevalence of hypertension to range from 20.4 [9] to 33.1% [11] in adults.

Hypertension and its complications are responsible for about 25% of emergency medical admissions in urban hospitals in Nigeria [12, 13]. However, the level of awareness of its detrimental effect is abysmally low [8] and contributed to the poor control of the disease. The Prospective Urban Rural Epidemiology study showed that despite high levels of hypertension worldwide, only 34% of Africans are aware of their hypertension status, only 31.3% receive any treatment and only 6.5% have their BP under control [14].

In Nigeria, treatment and control of hypertension is poor. A study conducted among hypertensives attending health facilities in Federal Capital Territory reported about 70% of patients were non-adherent to treatment [15] while another study in Northern Nigeria reported a similar proportion of hypertensives did not achieve blood pressure control [16]. Factors adduced for this poor outcome of treatment include those related to patients such as non-affordability of treatment cost, inadequate awareness and poor knowledge of hypertension, poor health-seeking behaviour, low compliance with scheduled follow-up visits and suboptimal pharmacotherapy and lack of trust in the healthcare system among others. Health system-related factors include lack of infrastructure/equipment/medicines, poor attitude, remuneration of health workers, lack of skilled/trained manpower, non-inclusion of hypertension treatment in primary healthcare function and inadequate facilities in the community [17]. The other factors include poverty, unhealthy dietary intake and sedentary lifestyle [17].

Currently there is a paradigm shift in the control of hypertension in line with community-based approach to the control of diseases, termed Community-clinical linkages, which is becoming a complementary strategy to existing health facility-based interventions in countries with limited health manpower and in remote communities. Community-clinical linkages are connections between community and clinical sectors to improve population health, foster community-clinic relationship and improve patient’s access to preventive and chronic care services [18]. This strategy has been used successfully in control of infectious diseases [references - proposal [19–21]], and the use in hypertension control is gaining ground in sub-Saharan Africa with some demonstration of promising benefits in reducing hypertension and changes in behaviour related to healthy lifestyle when CHWs implement community-based interventions [22–25]. A few interventions may be ongoing [26], and this proposed study stands to learn voice on /contribute to knowledge on the effectiveness of this strategy and share experience as conducted in Nigeria.

In Nigeria, CORPs are part of community-based care providers who are called differently as community health works, village health workers, village/community volunteers and community-based drug distributors among others depending on the setting. The use of this group of people in task sharing in Nigeria varies depending on location and need. In Nigeria, some lay persons who met stipulated criteria have been trained for this function and used in communities for different assignments such as for immunization campaign, mobilizers, health education, drug distribution, integrated community-based case management iCCM of febrile illness [27] and home management of malaria [26]. The use of community-based volunteers has also been carried out for interventions geared towards reduction of maternal deaths facilitating early presentation in pregnancy and adherence to clinic visits [28]. Furthermore, the strategy has been used under community-directed interventions (CDI) for ivermectin distribution for onchocerciasis and later for malaria and tuberculosis treatment [29].

## Conceptual framework

Precede-Proceed framework was considered suitable for the implementation of this project. This is because it focuses on three cardinal issues, which include the Predisposing, Enabling and Reinforcing factors. PRECEDE stands for Predisposing, Reinforcing, and Enabling Constructs in Educational Diagnosis and Evaluation. It involves social, epidemiological, ecological factors assessments; assessing the following community factors: PROCEED stands for Policy, Regulatory, and Organizational Constructs in Educational and Environmental Development. The issues concerning the individuals, community and the health system are well accentuated in the framework. The variables in the specific objectives of the projects are well captured in the framework. The PRECEDE-PROCEED model is a comprehensive structure for assessing health needs for designing, implementing and evaluating health promotion and other public health programmes to meet those needs [30]. PRECEDE provides the structure for planning a targeted and focused public health programme while PROCEED provides the structure for implementing and evaluating the public health programme.

### Objectives {7}

The study aims to evaluate the effectiveness of an intervention package on knowledge and control of high blood pressure, and reduction in hypertension risk factors among adults. The acceptability of CORPs and their effectiveness in delivering the intervention will also be assessed.

### Trial design {8}

This study will employ a cluster-randomized controlled trial and mixed method of data collection. It comprises of three phases: baseline, intervention and post-intervention: Baseline and endline surveys which will be conducted after 6 months of intervention in the control and intervention arms of the study. Information will be collected on socio-demographic variables, anthropometry measurements such as weight and height, clinical data and biochemical analysis of food sodium content, urinary salt and serum lipid profiles. Focus group discussion (FGD) for community members and key informant interviews (KII) for stakeholders at the health facilities and in the community will be conducted. A follow-up study will be implemented in the intervention arm deploying the intervention over a 6-month period after which effect on hypertension control and fidelity of implementation will be evaluated. The study design and flow chart are shown in Fig. 1.

**Fig. 1 Fig1:**
[figure not shown]
Study design and flow chart

## Methods: participants, interventions and outcomes

### Study setting {9}

The study will be conducted in three states selected from the six geopolitical zones in Nigeria comprising of Abia (South East), Kano (North West) and Oyo (South West) states. A state in Nigeria comprises a number of LGAs and each LGA is made up of 10 to 12 wards.

Two Local Government Areas (LGAs) (one urban and one rural) each were selected from each state based on participation in past hypertension survey and good cooperation received from the community members in past studies. Thus, in Abia State—Umuahia North (urban) and Isuikwuato (rural) with population of 292,300 and 151,700; in Kano state—Tarauni (Urban) and Bichi (Rural) with population of 387,100 and 308,600; and in Oyo state—Ibadan North (Urban) and Ona-Ara (Rural) with population of 473,900 and 373,100 respectively will be studied [31]. Figure 2 is the map of Nigeria showing selected states visited.

**Fig. 2 Fig2:**
[figure not shown]
Map of Nigeria showing the states selected for study

In the urban sites, the predominant economic activities are white- and blue-collar jobs, trading and other commercial activities. There are small-, medium- and large-scale industries and very little farming activities, whereas, in the rural sites, the people are predominantly farmers with few small-scale industries and trading.

The Local Government in each of the states has a Secondary/Comprehensive health facility, while each ward has a primary health facility (PHC). The PHCs are manned by a team of medical officer, nurses, community health extension workers, junior community health extension workers and pharmacy assistants headed by the medical officer or senior nurse where there is no medical officer.

Existing within the wards are trained lay persons who have served as community health workers at some point or participated in previous community-based studies such as the home management of malaria using artemisinin-based combination therapy study. Some will be selected from them to serve as CORPs. Where there are no CORPs, communities shall nominate persons who meet selection criteria to represent their communities.

### Eligibility criteria {10}

The study will involve two groups of participants: the community members and the CORPs.

#### Community members

The community members will participate at the three phases of the study.

For the base- and endline surveys, participants will be consenting residents of the community aged ≥18 years. A resident will be someone who has been living in the community for 6 months or more. Those who are sick at time of survey, mentally challenged or have communication challenge and pregnant women will be excluded from the survey. In addition, at endline survey, a subgroup of participants in the intervention arm will be randomly selected to participate in focus group discussions and in-depth interviews to explore their acceptability and perception of quality of the CORPs delivered follow-up care, as well as perceived challenges to implementation and sustainability.

For recruitment into the intervention, those found at community screening to have elevated blood pressure and same confirmed in the health facility, old patients receiving treatment and not controlled or not on treatment will be eligible for recruitment. They must plan to reside in the community for at least 1 year after enrollment and willing to participate in the home-based follow-up care by CORPs. To be excluded are patients with clinically established complications and other cardiovascular diseases, patients needing or on special medical services and pregnant women. The health workers to recruit at the health facilities will be medical officers of health and nurses involved in the care of adults in the health facilities. They will be trained on diagnosis, treatment and prevention of hypertension as well as use of the national guideline for treatment of hypertension.

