### Intervention description {11a}

The highlights of the activities and assessments for intervention and control arm are shown in Table 1. The components of the intervention include the following.

**Table 1 Tab1:** Highlights of the activities and assessments for intervention and control arm

	Activity	Intervention	Control
1	Baseline survey	Yes	Yes
2	Selection, screening and standard training of CORPs on blood pressure screening	Yes	Yes
3	Training on additional information on follow-up care for hypertensive patients and CORPs coordination	Yes	No
4	Trained CORPs screen and refer community members found to have high blood pressure	Yes Referral to the designated primary healthcare centre in the community	Yes Referral will be to the community member’s health facility of choice
5	Train health facility staff in designated primary healthcare facilities on the National guideline for hypertension treatment	Yes	No
6	CORPs Monthly checking and recording of blood pressure as well as providing health education/counselling support by the CORPs	Yes	No
7	SMS messaging on medication and healthy lifestyle adherence to support follow-up care	Yes	No
8	Anthropometry measurement, e.g. weight, height and body mass index (BMI) Biochemical measurement ECG	Yes	No
9	Endline survey	Yes	Yes

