### Outcomes {12}

The Primary outcomes are (i) change in baseline proportion of patients with controlled blood pressure, (ii) the mean change in blood pressure at 6 months between patients in the intervention and control communities. The secondary outcome measures are (i) change from baseline in proportion of patients adhering to medication, (ii) change in proportion of patients who are overweight/obese, smoke, take alcohol, practice unhealthy dietary habit and are physically inactive. In addition are (iii) mean improvement in quality-of-life score, (iv) percentage increase in satisfaction with care score, (v) change in awareness, knowledge, perception and practice, (vi) proportion of CORPs assessed to have good competency score, (vii) perception about quality and acceptability of home-based follow-up care delivered by CORPs, (viii) incidence of cardiovascular events among patients, (ix) change in baseline proportion of patients assessed to have high cardiovascular risk, (x) mean cost of treatment of hypertension, (xi) mean change in lipid level, urinary sodium and food sodium content. These variables will be measured at the end of the second, fourth and sixth month follow-up period.

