## Statistical methods

### Statistical methods for primary and secondary outcomes {20a}

Data analysis will be carried out using Stata MP version 14 based on the CONSORT 2010 guideline [40]. Intention-to-treat analysis will be applied. Continuous variable will be presented as mean and standard deviations (SDs) or medians with their 25th and 75th percentiles when the distribution of the data does not follow a Gaussian distribution. Categorical variables shall be presented as frequencies and percentages.

Baseline characteristics of participants in the intervention and control arms will be compared to assess balance and identify any variable that need to be adjusted in the final analysis. The primary outcome is achievement of blood pressure control at 6 months post-intervention. The effect of intervention within each of the study groups will be carried out comparing baseline and 6 months post-intervention using McNemar test. Depending on the distribution of baseline characteristics, random effect logit model will be fitted to estimate treatment effect size comparing the two groups. Similar analysis will be done for categorical secondary outcomes such as treatment adherence.

Cost-effectiveness analysis will also be carried out using the ingredient approach [41].

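### The protocol contradicts itself on whether enrolled control patients are individually re-measured at 6 months, which the patient-level primary comparison and the within-arm McNemar test both need

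*Protocol article*

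**What the plan says.** Three places in the protocol article point to no individual follow-up of control patients:

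- Trial design {8}: "A follow-up study will be implemented in the intervention arm deploying the intervention over a 6-month period".
- Table 1, under Intervention description {11a}, marks two assessment rows Yes for intervention and No for control: "CORPs Monthly checking and recording of blood pressure as well as providing health education/counselling support by the CORPs" and "Anthropometry measurement, e.g. weight, height and body mass index (BMI) Biochemical measurement ECG". After screening and referral, the only control activity marked Yes is the endline survey.
- Eligibility criteria {10} defines who is in that survey: "For the base- and endline surveys, participants will be consenting residents of the community aged ≥18 years". The abstract describes its purpose: "an endline survey will be conducted in both intervention and control communities to evaluate changes in mean BP, control, knowledge".

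Five places assume the opposite:

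- The abstract has 200 hypertensive patients per state followed for 6 months across both arms.
- Outcomes {12} defines a primary outcome as "the mean change in blood pressure at 6 months between patients in the intervention and control communities", and sets measurements at months 2, 4 and 6 without limiting them to one arm.
- The ECG section plans a start and an end recording for people with confirmed hypertension, with no arm limit.
- The specimens section {33} plans blood and urine tests at recruitment and at 6 months, again with no arm limit.
- Statistical methods {20a} assesses change within each study group by "comparing baseline and 6 months post-intervention using McNemar test".

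**The concern.** The primary outcomes and the paired test concern enrolled patients. They require blood pressure on the same people at two times, in both arms. The text that assigns activities to arms does not provide this for control.

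Other sections do not close the gap. Control patients are referred to a facility they choose themselves, so no designated study clinic would see them at 6 months. The retention plan {18b} and the missing-data section {20c} rely on home visits by the community-oriented resource persons (CORPs), and Table 1 gives the monthly visits to the intervention arm only.

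A field team working from Table 1 and the survey eligibility text could finish the trial without a 6-month reading on the enrolled control patients, and could not recover it afterwards.

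**Working it through.** This is mainly a reading of sections against each other. The arithmetic only fixes the number of patients concerned.

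**Step 1. How many control patients.** Sample size {14} gives 50 per arm in each LGA, hence 2 × 50 = 100 per LGA, 2 × 100 = 200 per state and 3 × 200 = 600 overall. This reproduces the stated total. The control arm is 6 LGAs × 50 = 300 patients. Whether 50 itself follows from the stated inputs is a separate question that does not bear on this point.

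**Step 2. What the analyses need.** McNemar's statistic is (b − c)² / (b + c), where b and c count patients whose control status changed in each direction. It needs each patient's status at both times; two separate samples give only the two marginal proportions. The change in blood pressure for patient i is BP at 6 months minus BP at baseline, which again needs both readings on that patient.

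**Step 3. What each section supplies for a control patient at 6 months.**

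| Section | Individual 6-month measurement in control? |
|---|---|
| Trial design {8} | Follow-up study placed in the intervention arm |
| Table 1, monthly BP recording | No |
| Table 1, anthropometry, biochemistry, ECG | No |
| Table 1, endline survey | Yes, but of adult residents by the {10} definition |
| Abstract, Methods | Yes, both arms |
| Outcomes {12} | Implied, months 2, 4 and 6 |
| ECG section and {33} | Implied, no arm limit; conflicts with Table 1 |
| Statistical methods {20a} | Required, pairs within each group |

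No section says who measures blood pressure in enrolled control patients at 6 months, or where.

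**Step 4. Could the survey supply the pairs by chance?** The protocol gives neither the endline sample size nor the adult population per community, so this is illustration only. Assume that the endline survey matches the baseline survey ("occurrence and risk factors of hypertension among 1704 adults ≥18 years"), is a random draw, and is spread evenly over 3 × 10 = 30 communities: 1704 / 30 = 56.8 people per community. With A adults per community, the expected number of the 300 control patients re-measured is 300 × 56.8 / A.

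| Assumed A | Expected control patients re-measured |
|---|---|
| 500 | 34.1 (11.4%) |
| 1,000 | 17.0 |
| 2,000 | 8.5 |
| 5,000 | 3.4 |
| 10,000 | 1.7 (0.6%) |

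Under these assumptions, a fresh resident sample would not supply the pairs. Enrolled patients would have to be traced deliberately.

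**The case against.** The strongest reply is that two-arm follow-up is already promised and that the one-arm text describes delivery of care. The follow-up study in Trial design {8} can be read as CORP home care, which is naturally one-armed, and monthly recording in Table 1 is part of the same package. The table is presented as highlights. The flow chart is not available here, and a condensed article may leave the logistics of re-measurement to operating procedures. Enrolled patients are adult residents and so are not excluded from the endline survey. The blinding section also mentions interviewers for a final assessment.

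Much of this stands. A reader might infer that the survey is the only 6-month contact with control patients, or that no control follow-up is planned. The documents do not support that: the abstract, Outcomes {12}, the ECG section and {33} all point the other way.

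A reader might also infer that an intervention cohort will be compared with a control cross-section, with a built-in difference as large as the planned effect. No section says so. The same endline survey is applied in both arms, and the primary outcome compares patients with patients.

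The reply does not remove the conflict. Table 1 does more than omit detail: it marks the anthropometry, biochemistry and ECG row No for control, while the ECG section and {33} set those tests without an arm limit. Being eligible for a survey is also not the same as being traced and re-measured in it.

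**Conclusion.** The point holds as an internal contradiction, to be reconciled before recruitment. Trial design {8}, the survey definition in {10} and Table 1 cannot all be followed together with the abstract, {12}, the ECG section, {33} and {20a}.

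If Table 1 and {10} govern:

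- The McNemar test lacks pairs in the control arm.
- The control side of the patient-level primary comparison, 300 planned patients, is not secured.
- A comparison of the two resident surveys would keep the community randomisation, but it would answer a community-level question. The 600 was set for recruited people living with hypertension, not for a sample of all adults.

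No numerical bias is claimed, because that would need an endline sample size and an asymmetric analysis that the protocol does not state. The conclusion rests on the wording of the sections and does not depend on the overlap illustration.

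**What to change.** - In Trial design {8}, Eligibility criteria {10} and Outcomes {12}, state that every enrolled patient in both arms is individually re-measured at 6 months by the endline interviewers, using the three-reading procedure in the Blood pressure section.
- State that the primary analysis uses this enrolled cohort in both arms, and that the resident survey serves community-level outcomes.
- Add a row to Table 1 for a 6-month patient assessment, marked Yes in both arms. Reconcile the anthropometry, biochemistry and ECG row with {12}, the ECG section and {33}.
- Record address and phone details for all enrolled patients. Recruitment {15} states this only for people found hypertensive in the baseline survey, not for those screened later or presenting at facilities.

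The cost is protocol wording, a contact list and some tracing work in control communities, where the endline survey is due to run anyway. The abstract already promises this follow-up, and Trial status says recruitment for the intervention had not begun, so the change can be made before any patient is affected.
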